**5.11. Detailed description of study stages/visits**

When materials are provided by GSK Biologicals, it is **MANDATORY** that all clinical samples (including serum samples) will be collected and stored using exclusively those materials in the appropriate manner. The use of other materials could result in the exclusion of the subject from the ATP analysis (See Section 10.6 for definition of study cohorts to be evaluated). The investigator must ensure that his/her personnel and the laboratory(ies) under his/her supervision comply with this requirement. However, when GSK Biologicals does not provide material for collecting and storing clinical samples, then appropriate materials from the investigator's site are to be used. Refer to Appendix D and Appendix E.

---

**Clinic Visit 1: Screening**  
Week -4 to Day 0

---

- Obtain signed, dated, thumb printed informed consent from the parent(s)/guardians
- Check inclusion/exclusion criteria
- Record HBV immunization status
- Take medical history and carry out physical examination
- Record any SAEs that may have occurred as a result of study procedures
- Venous blood sample to collect 5 mL blood for analysis of:
  - hematology (complete blood count)
  - biochemistry (creatinine, ALT and bilirubin)
  - serology (antibodies to CS, HBs)
  - cell-mediated immunity and B-cell memory

---

**Clinic Visit 2: Vaccination 1**  
Day 0

---

- Check study identification card of vaccinee
- Take medical history and carry out physical examination, measure body weight
- Check contraindications to vaccination
- Check elimination criteria
- Record pre-vaccination body temperature

- Randomize subjects
- Administer the first dose of RTS,S/AS01E or RTS,S/AS02D intramuscularly in the left deltoid

Each child will be assessed for at least 60 minutes after vaccination to evaluate and treat any acute adverse events.

- Record any post-vaccination solicited symptoms
- Record any post-vaccination unsolicited adverse events
- Record any post-vaccination SAEs
- Record concomitant medication

---

**Field worker post vaccination follow-up visits 21 to 25**  
Days 1, 2, 3, 4, and 5

---

- Record axillary temperature of subject
- Record local (pain and swelling at the injection site) and general (fever, irritability / fussiness, drowsiness, loss of appetite) solicited adverse events
- Record SAEs experienced by the vaccinee since the last visit
- Record unsolicited adverse events experienced by the vaccinee since the last visit
- Record concomitant medication

---

**Clinic Visit 3: Post Dose 1 follow-up visit in Clinic**  
Day 6

---

- Check study identification card of vaccinee
- Carry out physical examination
- Record axillary temperature of subject
- Record local (pain and swelling at the injection site) and general (fever, irritability / fussiness, drowsiness, loss of appetite) solicited adverse events
- Record SAEs experienced by the vaccinee since the last visit
- Record unsolicited adverse events experienced by the vaccinee since the last visit
- Check elimination criteria
- Record concomitant medication
- Blood sample to collect a minimum 1 mL blood for analysis of:
  - hematology (complete blood count)
  - biochemistry (creatinine, ALT and bilirubin)

**Clinic Visit 4: Vaccination 2**

Day 30

- Check study identification card of vaccinee
- Check contraindications to vaccination
- Check elimination criteria
- Record unsolicited adverse events experienced by the vaccinee since the last visit
- Record pre-vaccination body temperature
- Administer the second dose of RTS,S/AS01E or RTS,S/AS02D intramuscularly in the left deltoid

Each child will be assessed for at least 60 minutes after vaccination to evaluate and treat any acute adverse events.

- Record any post-vaccination solicited symptoms
- Record any post-vaccination unsolicited adverse events
- Record any post-vaccination SAEs
- Record concomitant medication

**Field worker post vaccination follow-up visits 26 to 31**

Days 31, 32, 33, 34, 35 and 36

- Record axillary temperature of subject
- Record local (pain and swelling at the injection site) and general (fever, irritability / fussiness, drowsiness, loss of appetite) solicited adverse events
- Record SAEs experienced by the vaccinee since the last visit
- Record unsolicited adverse events experienced by the vaccinee since the last visit
- Record concomitant medication

**Clinic Visit 5: Vaccination 3**

Day 60

- Check study identification card of vaccinee
- Check contraindications to vaccination
- Check elimination criteria
- Record unsolicited adverse events experienced by the vaccinee since the last visit
- Record pre-vaccination body temperature
- Administer the third dose of RTS,S/AS01E or RTS,S/AS02D intramuscularly in the left deltoid

Each child will be assessed for at least 60 minutes after vaccination to evaluate and treat any acute adverse events.

- Record any post-vaccination solicited symptoms
- Record any post-vaccination unsolicited adverse events
- Record any post-vaccination SAEs
- Record concomitant medication
- Blood sample to collect 5 mL blood for analysis of:
  - serology (antibodies to CS, HBs)
  - cell-mediated immunity and B-cell memory

---

**Field worker post vaccination follow-up visits 32 to 37**

Days 61, 62, 63, 64, 65 and 66

---

- Record axillary temperature of subject
- Record local (pain and swelling at the injection site) and general (fever, irritability / fussiness, drowsiness, loss of appetite) solicited adverse events
- Record SAEs experienced by the vaccinee since the last visit
- Record unsolicited adverse events experienced by the vaccinee since the last visit
- Record concomitant medication

---

**Clinic Visit 6**

Day 90

---

- Check study identification card of vaccinee
- Carry out physical examination
- Record axillary temperature of subject
- Record SAEs experienced by the vaccinee since the last visit
- Record unsolicited adverse events experienced by the vaccinee since the last visit
- Check elimination criteria
- Record concomitant medication
- Venous blood sample to collect 5 mL blood for analysis of:
  - hematology (complete blood count)
  - biochemistry (creatinine, ALT and bilirubin)
  - serology (antibodies to CS, HBs)
  - cell-mediated immunity and B-cell memory

---

**Field worker post vaccination follow-up visits 38 to 47**

Months 4, 5, 6, 7, 8, 9, 10, 11, 12, 13

---

- Record axillary temperature of subject
- Record concomitant medication

- Record SAEs experienced by the vaccinee since the last visit

---

**Clinic Visit 7: final study visit**

Month 14

---

- Record axillary temperature of subject
- Check elimination criteria
- Record concomitant medication
- Record SAEs experienced by the vaccinee since the last visit
- Venous blood sample to collect 5 mL blood for analysis of:
  - hematology (complete blood count)
  - biochemistry (creatinine, ALT and bilirubin)
  - serology (antibodies to CS, HBs)
  - cell-mediated immunity and B-cell memory

## **5.12. Sample handling and analysis**

### **5.12.1. Treatment and storage of biological samples**

See Appendix D of the protocol for details of treatment and storage of biological samples.

See Appendix E for instructions for shipment of biological samples.

### **5.12.2. Laboratory assays**

At the investigator center (trial site), the following will be performed:

- Hematology and biochemistry determination
- Separation of serum from the blood samples, and freezing for shipment
- Freezing of sample for CMI, for shipment
- B-cell memory assays

**Table 5 Laboratory immunological assays to be performed**

| Assay                  | Marker | Assay method   | Test Kit/ Manufacturer | Assay unit                 | Assay cut-off | Laboratory                                     |
|------------------------|--------|----------------|------------------------|----------------------------|---------------|------------------------------------------------|
| Anti-CS antibodies     | R32LR  | ELISA          | In-house ELISA*        | EU/mL                      | 0.5           | Leroux-Roels Laboratory, CEVAC, Ghent, Belgium |
| Anti-HBs antibodies    |        | EIA            | AUSAB EIA ABBOTT*      | mIU/mL                     | 10**          | GSK Biologicals†, Rixensart, Belgium           |
| Cell-mediated immunity |        | ICS            | In-house ICS           | % cytokine positive cells  |               | GSK Biologicals†, Rixensart, Belgium           |
| B-cell memory          |        | B-cell Elispot | In-house assay         | % antibody producing cells |               | HAS MRU                                        |

\*: or equivalent

\*\*: seroprotective level

†: or designated validated laboratory

ELISA: Enzyme-linked Immunoabsorbent Assay

EIA: Enzyme immunoassay

CEVAC: Center for Vaccinology, Ghent University

ICS: Intra-cellular cytokine staining

ELISPOT: Enzyme-linked Immuno-Spot

The GSK Biologicals' laboratory at Rixensart has established Quality Control Procedures and an established Quality System. Both are audited regularly for quality assessment by an internal (sponsor-dependent) but laboratory-independent Quality Department to document the competency of the facility to perform the required tests and support the reliability of the results. Methods and equipment are validated, where required.

### 5.12.3. Serology, CMI and B-cell memory plan

Serum for antibody determination, CMI and B-cell memory will be collected by blood sample. Details of the assay methodology can be found in Appendix F. Samples for safety will be analyzed at the time they are collected. All samples will be kept in a secure locked area at the investigator's site or GSK Biologicals (or designated validated laboratory). All samples will only be made available to authorized personnel.

In order to spare blood volumes collected from the children, CMI and B-cell memory immune responses will not be determined in the same children. Half of the children will have CMI assessed, and the other half will have B-cell memory immune response characterized. Attribution will be determined by a randomization list (1:1), balanced by study group.

Serology will be assessed in all children.

Serum and CMI samples will be shipped to GSK Biologicals, Rixensart, Belgium.

Any serum and cells not immediately used in antibody assays will be stored at -20°C or less. Stored samples could be anonymized and used to assess the immune response to vaccination or to assess any potential toxicity of the vaccine (details of serology testing

are given in Appendix F). All serum/cells samples will be destroyed within ten years of study completion.

**Table 6 Summary of blood sampling time points/immunological assays**

| Blood sampling time point |                |                  | Test                | No. subjects | Laboratory       | Priority ranking |
|---------------------------|----------------|------------------|---------------------|--------------|------------------|------------------|
| Timing                    | Study Month    | Clinic Visit No. |                     |              |                  |                  |
| Screening                 | Screening      | 1                | Anti-CS antibodies  | 180          | GSK Biologicals* | 1                |
|                           |                |                  | Anti-HBs antibodies | 180          | GSK Biologicals* | 2                |
|                           |                |                  | CMI                 | 90           | GSK Biologicals* | 3                |
|                           |                |                  | B-cell memory       | 90           | HAS MRU          | 4                |
| Post Dose 2               | Study Month 2  | 5                | Anti-CS antibodies  | 180          | GSK Biologicals* | 1                |
|                           |                |                  | Anti-HBs antibodies | 180          | GSK Biologicals* | 2                |
|                           |                |                  | CMI                 | 90           | GSK Biologicals* | 3                |
|                           |                |                  | B-cell memory       | 90           | HAS MRU          | 4                |
| Post Dose 3               | Study Month 3  | 6                | Anti-CS antibodies  | 180          | GSK Biologicals* | 1                |
|                           |                |                  | Anti-HBs antibodies | 180          | GSK Biologicals* | 2                |
|                           |                |                  | CMI                 | 90           | GSK Biologicals* | 3                |
|                           |                |                  | B-cell memory       | 90           | HAS MRU          | 4                |
| Post Dose 3               | Study Month 14 | 7                | Anti-CS antibodies  | 180          | GSK Biologicals* | 1                |
|                           |                |                  | Anti-HBs antibodies | 180          | GSK Biologicals* | 2                |
|                           |                |                  | CMI                 | 90           | GSK Biologicals* | 3                |
|                           |                |                  | B-cell memory       | 90           | HAS MRU          | 4                |

\*: or designated laboratory

## 6. INVESTIGATIONAL PRODUCTS AND ADMINISTRATION

### 6.1. Study vaccines

The candidate vaccines to be used have been developed and manufactured by GSK Biologicals. A summary of details relating to the study vaccines can be found in Table 7.

The Quality Control Standards and Requirements for the candidate vaccine are described in separate release protocols and the required approvals have been obtained.

Refer to Appendix G for details of vaccine supplies.

**Table 7 Details of study vaccines to be administered during trial**

| Vaccine     | Formulation                                                                | Presentation                                                                                                            | Volume | N° doses*                  |
|-------------|----------------------------------------------------------------------------|-------------------------------------------------------------------------------------------------------------------------|--------|----------------------------|
| RTS,S/AS01E | RTS,S 25 µg
MPL 25 µg
QS21 25 µg
Sucrose
Liposomes             | RTS,S and sucrose pellet in 3 mL monodose vial
Adjuvant provided in monodose vial
Opalescent reconstituted liquid | 0.5 mL | Sufficient for 90 subjects |
| RTS,S/AS02D | RTS,S 25 µg
MPL 25 µg
QS21 25 µg
Sucrose
Oil-in-water emulsion | RTS,S and sucrose pellet in 3 mL monodose vial. Prefilled adjuvant syringes. Milky reconstituted liquid                 | 0.5 mL | Sufficient for 90 subjects |

\*: In addition to the vaccine doses provided for the planned number of enrolled subjects, 3% additional doses will be supplied in case a vaccine dose is broken or unusable

### 6.1.1. RTS,S/AS01E vaccine

The final RTS,S/AS01E vaccine consists of two fractions: the lyophilized fraction containing the RTS,S antigen in one vial and the liquid fraction, consisting of AS01E adjuvant in the other vial to be used for reconstitution just prior to injection. A dose of 0.5 mL will be injected. The presentation of the reconstituted RTS,S/AS01E candidate malaria vaccine is an opalescent liquid.

#### 6.1.1.1. RTS,S antigen presentation:

- The RTS,S antigen presents as a lyophilized pellet containing approximately 25 µg of antigen with sucrose as cryoprotectant per 3 mL monodose vial.

#### 6.1.1.2. AS01E adjuvant:

- AS01E contains 25 µg of MPL, 25 µg QS21 (QS21 is a triterpene glycoside purified from the bark of *Quillaja saponaria*) with liposomes.

### 6.1.2. RTS,S/AS02D vaccine

The final RTS,S/AS02D vaccine consists of two fractions: the lyophilized fraction containing the RTS,S antigen in one vial and the liquid fraction, consisting of AS02D adjuvant in pre-filled syringes to be used for reconstitution just prior to injection. A dose of 0.5 mL will be delivered. The presentation of the reconstituted RTS,S/AS02D candidate malaria is an opaque milky liquid.

#### 6.1.2.1. RTS,S antigen presentation:

- The RTS,S antigen presents as a lyophilized pellet containing approximately 25 µg of antigen with sucrose as cryoprotectant per 3 mL monodose vial.

**6.1.2.2. AS02D adjuvant:**

- AS02D contains 25 µg of MPL, 25 µg QS21 (QS21 is a triterpene glycoside purified from the bark of *Quillaja saponaria*) and 125 µl of a proprietary oil-in-water emulsion and phosphate buffered saline per 0.5 mL, presented in prefilled syringes (PFS).

**6.2. Dosage and administration**

The vaccinees will be observed closely for at least 60 minutes following the administration of vaccines, with appropriate medical treatment readily available in case of an anaphylactic reaction.

**6.2.1. RTS,S/AS01E**

RTS,S/AS01E will be supplied such that the reconstituted vaccine volume will provide a 0.5 mL pediatric dose. One 0.5 mL dose will be withdrawn from each vial and used.

Disinfect top of vaccine vial (pellet) and adjuvant vial with alcohol swabs and let dry. Withdraw the contents of the adjuvant vial in a syringe and inject adjuvant into the vial of lyophilized antigen. Remove and discard the syringe and needle under appropriate safety precautions. The pellet is then dissolved by gently shaking the vial. Wait for 1 minute to ensure complete dissolution of vial contents before withdrawing a sufficient volume to provide a 0.5 mL dose (volume required for RTS,S/AS01E) of the reconstituted vaccine solution using a fresh needle and syringe for injection. The reconstituted vaccine should be administered by slow intramuscular (IM) injection, using a 25G needle with length of 1 inch (25 mm), in the left deltoid muscle within 4 hours of reconstitution (storage at +2°C to +8°C).

**6.2.2. RTS,S/AS02D**

RTS,S/AS02D will be supplied such that the reconstituted vaccine volume will provide a 0.5 mL pediatric dose. One 0.5 mL dose will be withdrawn from each vial and used.

Disinfect top of vaccine vial (pellet) with alcohol swabs and let dry. Inject complete contents of one PFS of adjuvant into vial of lyophilized vaccine. Remove and discard the syringe and needle under appropriate safety precautions. The pellet is then dissolved by gently shaking the vial. Wait for 1 minute to ensure complete dissolution of vial contents before withdrawing a sufficient volume to provide a 0.5 mL dose (volume required for RTS,S/AS02D) of the reconstituted vaccine solution using a fresh needle and syringe for injection. The reconstituted vaccine should be administered by slow IM injection, using a 25G needle with length of 1 inch (25 mm), in the left deltoid muscle within 4 hours of reconstitution (storage at 2°C to 8°C).

### **6.3. Storage**

**ALL VACCINE VIALS/PRE-FILLED SYRINGES AND ADJUVANTS MUST BE STORED IN THE REFRIGERATOR (+2°C to +8°C) AND MUST NOT BE FROZEN.**

All vaccines will be stored in a safe and locked place with no access for unauthorized personnel. Storage temperature will be monitored three times daily, according to SOPs at the investigator's site. An alarm system and a back-up refrigerator will be available in case of power failure/breakdown.

The study monitor must be contacted if the cold chain is broken (e.g. vaccines become frozen or refrigeration fails).

Storage conditions for transport of vaccines from country medical department or dispatch center to study sites or between sites are described in Appendix D.

### **6.4. Treatment allocation and randomization**

#### **6.4.1. Randomization of supplies**

A randomization list will be generated at GSK Biologicals, Rixensart, using a standard SAS® (Statistical Analysis System) program and will be used to assign the vaccines in a 1:1 fashion to treatment numbers.

#### **6.4.2. Randomization of subjects**

Subjects will be allocated sequentially to treatment numbers in the order that they present for vaccination.

### **6.5. Method of blinding and breaking the study blind**

Data pertaining to RTS,S/AS02D or RTS,S/AS01E will be collected in a double blinded (observer blinded) manner. 'Double blinded (observer blinded)' means that the vaccine recipient and their parent(s)/guardian(s) as well as those responsible for the evaluation of safety and immunogenicity endpoints will all be unaware which treatment, RTS,S/AS02D or RTS,S/AS01E, was administered to a particular subject. The only study staff aware of the vaccine assignment for RTS,S/AS02D or RTS,S/AS01E will be those responsible for the storage and preparation of vaccines; these staff will play no other role in the study.

Code break envelopes, for each study enrolled subject and associating each treatment number with a specific vaccine, will be kept by the Local Safety Monitor in Gabon as well as by Central Safety at GSK Biologicals, Rixensart in a safe and locked place with no access for unauthorized personnel.

If deemed necessary for reasons such as safety, the Local Safety Monitor in Gabon as well as GSK Biologicals Central Safety will unblind the specific enrolled subject without revealing the study blind to the investigators.

As part of the safety monitoring plan, safety reports will be produced at two timepoints in the trial (refer to 5.1.3.3). An independent statistician will analyze the data, thereby maintaining the blind of the malaria project team at GSK Biologicals and the investigator group.

A formal reporting and analysis plan (RAP) will be developed. Once the study is completed and the GSK Biologicals reference database locked, GSK Biologicals will be responsible for initiating the execution of the statistical analysis plan in collaboration with HAS and MVI and breaking the blind.

GSK Biologicals' policy (incorporating ICH E2A guidance, EU Clinical Trial Directive and Federal Regulations) is to unblind any serious adverse event (SAE) report associated with the use of the investigational product, which is unexpected and attributable/suspected, prior to regulatory reporting. The Clinical Safety Physician is responsible for unblinding the treatment assignment in accordance with specified time frames for expedited reporting of SAEs (Refer to Section 8.8).

## **6.6. Replacement of unusable vaccine doses**

Additional vaccine doses will be provided to replace those that are unusable (see Appendix G for details of supplies).

In addition to the vaccine doses provided for the planned number of enrolled subjects, 3% additional doses will be supplied. In case a vaccine dose is broken or unusable, the investigator should replace it with a replacement vaccine dose. If a vaccine dose needs replacement, the envelope with the corresponding treatment number will designate the replacement without unblinding the study using a coded letter system. Although the sponsor need not be notified immediately in these cases, documentation of the use of the replacement vaccine must be recorded by the investigator on the vaccine administration page of the CRF and on the vaccine accountability form.

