Vaccines will be administered in a blinded fashion. For each vaccination during the course of the study, the Vaccine Preparer will prepare the vaccine and the Vaccinator administer the vaccine for a specific subject. Since the vaccines used in this study are of distinct appearance, the Vaccine Preparers are not blinded and together with the Vaccinators perform no other function in the study (refer to Section 6.5). The Vaccine Preparer will select the sealed box labeled with the subject's treatment number, containing the vials numbered with the treatment number, remove the vaccine vials and fill a syringe according to this study protocol (refer to Section 6.2). The Vaccine Preparer will then place a numbered opaque label with the subject's treatment number on the syringe. The purpose of masking the syringe is to blind the parent(s) or guardians(s) of the subject. The Vaccine Preparer will then pass the syringe to the Vaccinator in an adjacent room who will administer the vaccination. After administering the vaccination to the subject the Vaccinator will enter the treatment number administered to the subject on the clinic form.

Subjects who cannot be vaccinated on the originally scheduled date (see Section 4.9.1) will be vaccinated within 7 days and undergo all study procedures for the visit on the same day as vaccination. In the particular case of any child found to be febrile (axillary temperature  $\geq 37.5^{\circ}\text{C}$ ), a blood slide will be taken to investigate for malaria. Children will be treated as appropriate for their condition and will be followed up until resolution of any symptoms and be vaccinated if their clinical symptoms resolve within 7 days.

Those who cannot be re-vaccinated within 7 days of their scheduled date will continue all study procedures apart from receiving further study vaccinations.

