### **1. Vaccine supplies**

GSK Biologicals will supply the following amounts of numbered doses of study vaccines, sufficient to administer 3 doses to all subjects as described in the present protocol.

- Sufficient doses for 90 recipients of the candidate vaccine RTS,S/AS02D (doses of RTS,S vaccine in monodose vials and doses of AS02D adjuvant in pre-filled syringes).
- Sufficient doses for 90 recipients of the candidate vaccine RTS,S/AS01E (doses of RTS,S vaccine in monodose vials and doses of AS01E adjuvant in pre-filled syringes).

An additional 3% of their respective amounts of RTS,S/AS02D and RTS,S/AS01E will be supplied for replacement in case of breakage, bad storage conditions or any other reason that would make the vaccine unusable (i.e., given by mistake to another subject).

All pre-filled syringes and vials must be accounted for on the form provided.

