### **3. Vaccine accountability**

The investigator or pharmacist must sign a statement that he/she has received the clinical supplies for the study. At all times the figures on supplied, used and remaining vaccine doses should match. At the end of the study, it must be possible to reconcile delivery records with those of used and unused stocks. An explanation must be given of any discrepancies.

After approval from GSK Biologicals, used vaccine vials/syringes should be destroyed at the study site using locally approved biosafety procedures and documentation unless otherwise described in the protocol. If no adequate biosafety procedures are available at the study site, the used vaccine vials/syringes are to be returned to an appropriate GSK Biologicals site for destruction in accordance with current GSK SOP WWD-1102. Unused vaccine vials/syringes will be disposed at the local GSK Biologicals site in accordance with GSK SOP WWD-1102. If no processes for destruction of unused

vaccines are in place in the local GSK Biologicals site; the unused vials/syringes must be returned to GSK Biologicals in Rixensart, Belgium.

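### Section 6.6 gives the investigator a dose-replacement task that Sections 5.4 and 6.5 reserve for unblinded staff, so a blinded evaluator could see which vaccine a few children received

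*Protocol*

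**What the plan says.** **Who must be blind.** Protocol Section 6.5 states that "those responsible for the evaluation of safety and immunogenicity endpoints will all be unaware which treatment" was given. It then limits who may know: "The only study staff aware of the vaccine assignment for RTS,S/AS02D or RTS,S/AS01E will be those responsible for the storage and preparation of vaccines", and adds that "these staff will play no other role in the study".

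**Why preparation is separated.** Section 5.4 gives the reason: "Since the vaccines used in this study are of distinct appearance, the Vaccine Preparers are not blinded". The Preparer opens the sealed box, fills the syringe and masks it. The Vaccinator injects in an adjacent room. Neither does anything else in the trial.

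**Who replaces a dose.** Section 6.6 says: "In case a vaccine dose is broken or unusable, the investigator should replace it with a replacement vaccine dose". An envelope bearing the treatment number points to the replacement through a letter code, which the section says preserves the blind. The investigator then documents the replacement on the CRF and on the accountability form.

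**Supplies.** Appendix G, item 1, says: "All pre-filled syringes and vials must be accounted for on the form provided". It names no role. Item 3 says: "The investigator or pharmacist must sign a statement that he/she has received the clinical supplies for the study".

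**Appearance.** Table 7 describes RTS,S/AS02D with the words "Prefilled adjuvant syringes. Milky reconstituted liquid". For RTS,S/AS01E it gives an adjuvant vial and an opalescent liquid.

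**The concern.** Selecting and handling a replacement dose belongs to storage and preparation. Section 6.6 gives that task to the one role that most needs to stay blind. Under Section 8.5.2 the investigator assesses the causality of every AE and SAE except solicited local reactions, which are counted as related by rule. Under Sections 5.1.3.3 and 5.1.3.4 the investigator also judges whether a fever above 39.0°C is related to vaccination, and that judgment feeds a suspension criterion.

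Under Section 5.4 a child keeps one treatment number for all doses. An investigator who recognises the product once therefore knows that child's assignment for the rest of the trial. A site that follows Section 6.6 to the letter could breach Section 6.5 without noticing.

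**Working it through.** The plan states no figure on this point to reproduce. The check is a comparison of the texts, followed by a bound on size.

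**1. Can one person satisfy both rules?**
- Sections 5.4 and 6.5: whoever stores or prepares vaccine may know the assignment and may have no other role.
- Section 6.6: the investigator replaces the dose.
- Section 8.5.2: the investigator assesses causality.
- If replacing includes handling the dose, the three cannot all hold for the same person. If it means only authorising and recording, they can. Section 6.6 does not say which is meant.

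**2. Is the product recognisable?**
- Sealed: no. Section 5.4 has identical boxes labelled by treatment number.
- Opened or broken: yes. Sections 6.1.1 and 6.1.2 describe the reconstituted liquids as opalescent (AS01E) and opaque milky (AS02D).
- Container: Table 7 and Sections 6.1.1 and 6.2.1 put the AS01E adjuvant in a vial, and Section 6.1.2 puts the AS02D adjuvant in a pre-filled syringe. Appendix G, item 1, puts both adjuvants in pre-filled syringes. On that text the container would not tell the vaccines apart, but the liquids still would.

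**3. How many children?** Inputs: 90 recipients per vaccine and 3 doses each (Appendix G), and 3% spare doses (Section 6.6).
- Doses per vaccine: 90 × 3 = 270.
- Spares per vaccine: 0.03 × 270 = 8.1, so about 8, or 9 if rounded up to whole doses.
- Both vaccines: 2 × 8.1 = 16.2, so about 16 (18 if rounded up).
- Share of children: 16/180 = 8.9% (18/180 = 10%).

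This is a ceiling. It requires every spare to be used, each for a different child, with the contents seen each time.

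**4. What about the fever criterion?** The safety reports cover the first 40 children after Doses 1 and 2, which is 80 doses.
- If doses were replaced at the 3% supply rate (an assumption): 0.03 × 80 = 2.4, so about 2 replaced doses.
- If the 40 children split evenly (an assumption), each vaccine has 20 doses per report, or 40 over both doses. The criterion is more than 5% of doses. One fever in 20 is 5.0%, which does not cross it, and two in 20 is 10%, which does. Two in 40 is 5.0%, and three in 40 is 7.5%.

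A single relatedness judgment can therefore decide whether the criterion is met, but few such judgments would concern a child with a replaced dose.

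**5. Which endpoints depend on the judgment?**
- Coprimary safety (Sections 10.1.1 and 10.8.1.1): proportion of subjects with an SAE by preferred term, whatever the causality.
- Coprimary immunogenicity (Section 10.1.2): a laboratory titer.
- Secondary safety (Section 10.8.1.2): tables by relationship to vaccination. These depend on it.

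**The case against.** The best defence is that Section 6.6 should be read together with Section 5.4. The Preparer's duties apply to every vaccination in the study, so the Preparer would open the replacement box too, while the investigator documents the event. The letter code is there so that naming a replacement reveals nothing, and the boxes are identical. On this reading nobody is unmasked, and no passage says that the investigator sees opened contents. For the fever criterion there is a further check: the DSMB receives an unblinded report from an independent statistician and reviews the relatedness of all Grade 3 fevers.

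Much of this stands. The safeguards work up to the moment a box is opened. But a dose may be found broken or unusable only after opening, and the sentence naming who replaces it names the investigator. The defence needs the reader to override that sentence.

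Three stronger readings are tempting, and the documents do not support them.
- A reader might infer that the investigator must account for every syringe and vial, so that all 180 children could be unmasked. Appendix G names no role for that accounting and lets a pharmacist sign for receipt. Section 6.6 has the investigator record only the use of a replacement. Signing for sealed, identical boxes need not reveal an assignment.
- A reader might infer that one sighting unmasks every child who shares a code letter. The protocol does not say how letters are allocated or whether they repeat.
- A reader might infer bias in the coprimary safety comparison. That comparison counts SAEs regardless of causality.

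**Conclusion.** The conflict of roles holds. Taken literally, Section 6.6 brings a blinded evaluator into contact with distinguishable product, against Sections 5.4 and 6.5. It is an exposure of the blind with a partial safeguard, not a demonstrated break.

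The size is limited to at most about 16 of 180 children (9%), under the ceiling assumptions that all spares are used, each for a different child, and that the contents are seen each time. The realistic number is probably well below that. The exposure falls mainly on the secondary tables of related events and on the fever suspension criterion. The SAE count and the anti-CS non-inferiority comparison are not materially touched.

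The change is worth making because it is specific and costs almost nothing. The conflict over the AS01E adjuvant container is a separate documentary inconsistency, and the role conflict does not depend on how it is resolved.

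**What to change.** - **Section 6.6:** have the unblinded Vaccine Preparer, or a pharmacist with no evaluation role, select and handle the replacement and complete the accountability form. Pass only the treatment number and the replacement code to the investigator for the CRF.
- **Appendix G:** name the same unblinded role for any accountability that involves opened boxes or used containers. Signing for sealed supplies can stay as it is.
- **Separately:** reconcile the AS01E adjuvant presentation in Appendix G, item 1 (pre-filled syringes) with Table 7 and Sections 6.1.1 and 6.2.1 (vial).

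The cost is a few sentences and an entry in the delegation log. The unblinded role already exists, and no schedule, sample size or analysis changes. The one drawback is that the investigator would not see accountability records for opened containers while the blind is in force.
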